**Study procedures**

***Recruitment***

A banner link will be posted on the Blued’s portal website and startup screen. Recruitment announcements of the study will also be sent via other social media portals (WeChat; Weibo, a microblogging platform; and QQ, a messaging platform).

***Randomisation and allocation***

We will use block randomization with a block size of 12. Computer-generated randomisation codes will be produced and kept by a biostatistician who is not involved in participant enrollment.

Participant enrollment will be carried out online by a research assistant. Interested participants give consent and complete eligibility screening. Eligible participants then complete a baseline survey. Participants who complete the baseline survey are directed to contact the research assistant who is responsible for allocating the participants into one of the three intervention arms based on the randomization code. Participants will be provided with 20 RMB (equal to 3 US Dollars) for their time to complete the baseline survey.

***Blinding***

As it would not be possible to blind participants to their study arms, this is a single blinded study. Investigators and staff assessing the outcomes will be blinded to participants' group assignments.

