**Abstract**

**Background:** Men who have sex with men (MSM) bear a high burden of syphilis infection. Expanding syphilis testing to improve timely diagnosis and treatment is critical to improve syphilis control. However, syphilis testing rates remain low among MSM, particularly in low- and middle-income countries. We describe the protocol for a randomised controlled trial (RCT) to assess whether provision of syphilis self-testing services can increase the uptake of syphilis testing among MSM in China.

**Methods:** 444 high-risk MSM will be recruited online and randomized in a 1:1:1 ratio to (1) standard syphilis self-testing arm; (2) a self-testing arm program enhanced with crowdsourcing and a lottery-based incentive, and (3) a standard of care (control). Self-testing services include a free syphilis self-test kit through the mail at monthly intervals. Participants in the lottery incentive arm will additionally receive health promotion materials generated from an open crowdsourcing contest and be given a lottery draw with a 10% chance to win 100 RMB (approximately 15 US Dollars) upon confirmed completion of syphilis testing. Syphilis self-test kits have step-by-step instructions and an instructional video. This is a non-blinded, open-label, parallel RCT. Participants in each arm will be followed-up at three and six months through WeChat (a social media app like Facebook messenger). Confirmation of syphilis self-test use will be determined by requiring participants to submit a photo of the used test kit to study staff via secure data messaging. Both self-testing and facility-based testing will be ascertained by sending a secure photographic image of the completed kit through an existing digital platform. The primary outcome is the proportion of participants who tested for syphilis in the past three months.

**Discussion:** Findings from this study will provide much needed insight on the impact of syphilis self-testing on promoting routine syphilis screening among MSM. The findings will also contribute to our understanding of the safety, effectiveness and acceptability of syphilis self-testing. These findings will have important implications for self-testing policy, both in China and internationally.

**Trial registration:** ChiCTR1900022409 (10 April, 2019)

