**Study design**

This is a non-blinded, open-label, parallel RCT with individuals randomized in a 1:1:1 ratio to three study arms: control arm (standard of care); standard syphilis self-testing arm; and lottery incentivized syphilis self-testing arm. Control arm participants will receive information on self-referral pathways for free facility-based syphilis testing. Both self-testing arms will be offered to access syphilis self-test kits for free at monthly intervals. Participants in each arm will be followed-up for six months (Figure 1). The study hypothesis had been tested in a pilot study, completed in October 2019, which examined the feasibility of implementing the self-testing and crowdsourced lottery incentivized syphilis self-testing model among 145 Chinese MSM. The pilot study showed that both standard self-testing arm (0.74) and lottery incentivized arm (0.70) increased the frequency of syphilis testing more than the control arm (0.36). Preliminary data from this pilot study was used to inform this definitive trial design. Preliminary results are available on the supplement materials. The definitive trial, outlined in the current trial protocol, has begun in December 2019, and is expected to be completed in July 2020.

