The major challenge of this study is to retrieve validated testing proof to verify self-testing results. Our previous study reported that 47% of men submitted proof of syphilis self-testing with 20 RMB (about 3 US dollar) cash incentive [[18](#_ENREF_18)]. This was a cross sectional survey, and people are not always able to find the required proof, especially for those who tested a long time ago. Furthermore, we cannot guarantee that submitted photographic proofs truly belongs to the patient. We previously found that more than 30% of men would submit a proof of testing even if no incentive was offered in an HIV self-testing study [[25](#_ENREF_25)]. To increase the retrieval rate, we will provide a small cash incentive (5 RMB) to reimburse their submission of self-testing results or other testing proof materials. To link self-test kits with the user, we will code each self-testing package and direct them to take a photo of the used strip with the background of the package, which has been successfully tested in our pilot trial.

Another potential limitation of this study is the possibility of contamination between arms. We cannot prevent participants from the control arm to purchase syphilis self-testing kits for use through online e-market which we have been previously found in some MSM in China [[18](#_ENREF_18)]. To mitigate this, we will record the participants’ testing method in each group and if necessary adjust for this in the data analysis. The six-month duration of follow-up also limits the ability of the study to assess the long-term effect of the intervention on syphilis incidence.

Findings from this proposed study will be used to inform the design of a new syphilis self-testing model, which will be implemented alongside the traditional facility-based testing service to increase syphilis screening among MSM in China. We anticipate that the model will increase early syphilis diagnosis and enhance syphilis continuum of care and treatment for MSM, and ultimately reduce the spread of syphilis and HIV transmission among MSM and other individuals within their sexual networks in China.

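### The protocol calls the trial non-blinded but also claims blinded outcome assessors, and the self-test photos it describes rule out that blinding for self-testing versus control

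*Protocol*

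**What the plan says.** **Blinding.** The Protocol abstract states "This is a non-blinded, open-label, parallel RCT", and the Study design section repeats this: "This is a non-blinded, open-label, parallel RCT with individuals randomized in a 1:1:1 ratio to three study arms". The Blinding section then says "As it would not be possible to blind participants to their study arms, this is a single blinded study" and continues "Investigators and staff assessing the outcomes will be blinded", that is, to the arm of each participant.

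**Outcome evidence.** Under Outcomes Measures, the primary outcome is photo-verified in all participants. Data collection accepts a photo of the used kit for a self-test and a photo of the report for a facility test. The Discussion adds, for self-tests, "we will code each self-testing package and direct them to take a photo of the used strip with the background of the package". According to Arms and Interventions and Table 1, study packages go only to the two self-testing arms. An uploaded proof also earns a lottery draw in one arm only.

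**Allocation.** The section Randomisation and allocation states "We will use block randomization with a block size of 12". A biostatistician outside enrolment produces and holds the codes. A research assistant enrols online. After consent, screening and the baseline survey, participants contact the "research assistant who is responsible for allocating the participants into one of the three intervention arms based on the randomization code". The section does not say how codes reach the assistant, or whether the assistant knows the block size.

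**The concern.** A report that follows the Blinding section would describe the outcome as assessor-blinded; one that follows the Abstract would not. Both cannot be right. Assessor blinding matters here because some judgement goes into accepting a proof. The Discussion names the retrieval of valid proof as the major challenge and concedes that a photo may not belong to the person who sent it. If the person accepting proofs can tell a self-testing participant from a control, then blinding does not protect that comparison, which is the one the first study objective rests on.

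A second, smaller issue concerns allocation. In an open trial with one fixed block size, someone who both enrols and allocates may be able to work out some upcoming assignments.

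**Working it through.** **1. Are the labels compatible?** Open-label alone can coexist with blinded assessors, because it commonly means that participants and providers know the treatment. Non-blinded cannot, since it says that nobody is masked. The Abstract and Study design use both words and the Blinding section says single blinded, so the contradiction lies in the word non-blinded.

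**2. What does each type of proof tell an assessor?**

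| Proof submitted | Control vs self-testing | Standard vs lottery |
| --- | --- | --- |
| Used strip against coded study package | Revealed: controls are not sent this package | Not revealed, unless the code carries the arm (not stated) |
| Facility test report | Not revealed by the report itself | Not revealed |
| Kit bought online, no study package | Not revealed | Not revealed |

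The first row is the trial's own route for proving a self-test, so the claim fails exactly where the intervention works as intended.

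**3. Do other procedures work against masking?** Three do, for any assessor who handles them:
- The follow-up surveys put extra questions about kit use to the two self-testing arms only (Surveys).
- An accepted upload leads to a lottery draw in one arm only (Table 1).
- The Analysis plan excludes confirmatory tests after a reactive self-test, so someone must link a clinic report to the participant's self-test history before counting it.

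The protocol describes no step that masks photos before they are judged.

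**4. How predictable is the allocation?** Inputs are a block size of 12 and a 1:1:1 ratio (hence 4 per arm per block), with a total of 444 from the Sample size section. The number of complete blocks is 444/12 = 37. The calculation assumes that the allocator knows the block size, remembers all past assignments and does not see the list.

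- *Fully determined assignments.* An assignment is certain once only one arm is left in the block. The expected number is the expected length of the final run of identical assignments. Given the arm in the last position, 3 places of that arm remain among the other 11, and the 8 places of the other arms create 9 gaps. The expected run is 1 + 3/9 = 1.33 per block. That is 1.33/12 = 11.1%, and 37 × 1.33 = 49.3, or about 49 of 444.
- *Control versus a kit arm known for certain.* With probability 4/12 the last place is control, and the expected run is 1 + 3/9 = 1.333. With probability 8/12 it is a kit arm, and the expected run is 1 + 7/5 = 2.4. The mean is 0.444 + 1.600 = 2.044 per block, which is 17.0%, or about 76 of 444.
- *Best guess.* Exact enumeration of the block gives 6.144 correct guesses per 12, or 51.2%, against 33.3% by chance.

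The protocol states no figure of its own on this point, so there is none to reproduce.

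**The case against.** **On blinding.** A reader might infer that the photos reveal the arm outright. The document does not support that. A study package rules out control but does not separate standard from lottery. The Discussion says only that packages are coded to link kit and user, not that the code carries the arm. Facility reports carry no arm label as described. It is also fair to say that the presence or absence of a photo leaves an assessor limited discretion, and no section describes graded judgement of unclear images. All of this stands, and it is why masking of standard versus lottery remains possible. It does not rescue the claim for control versus self-testing.

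**On allocation.** A reader might infer that the assistant holds the list, or that a promised protection against selection is absent. Neither is shown. The protocol makes no explicit concealment claim, and one person can keep a list while releasing codes to another. Consent, screening and a self-administered online survey all precede allocation, which leaves little room to admit people selectively. What remains is a contact with the assistant just before assignment, an unstated method of code release, and partial predictability. The figures of 11% and 51% measure predictability under stated assumptions. They do not measure bias.

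**On timing.** The trial began in December 2019 with six months of follow-up and expected completion in July 2020, so enrolment would have to end around January 2020. A change to the randomisation list may reach few participants or none. The blinding statement still needs correcting before results are reported.

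**Conclusion.** The blinding point holds. The protocol contradicts itself on whether anyone is blinded, and it claims assessor blinding that its own photo procedure defeats for self-testing versus control. This rests on the text alone. The size of any resulting bias cannot be derived from the document.

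The allocation point is secondary and conditional. If the enrolling assistant knows the block size of 12 and tracks past assignments, about 11% of assignments (about 49 of 444) are fully predictable. Independent custody of the codes and the order of enrolment steps limit the scope for selection. To conclude that protection against bias is absent altogether would go beyond the text.

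**What to change.** **Blinding.** Use one statement in the Abstract, Study design and Blinding sections: the trial is open-label. Drop the claim that assessors are blinded to control versus self-testing. Claim masking only for standard versus lottery, and describe how it is achieved:
- package codes that do not reveal the arm;
- photos judged against a fixed checklist;
- judgement by existing staff who have no access to the arm list or the lottery records.

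The cost is a wording change, a check or relabelling of the codes, and a separation of tasks among existing staff.

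**Allocation, for any remaining enrolment.** The biostatistician releases one code at a time, after completion of the baseline survey has been logged, from a list with undisclosed, varying block sizes. Non-disclosure is essential. With k per arm, the same reasoning gives 3k/(2k + 1) determined assignments per block. A known block of 9 would give (9/7)/9 = 14.3% and a known block of 6 would give (6/5)/6 = 20.0%, both worse than 11.1% for 12. The cost is a regenerated list, a small logistic step and possibly slightly unequal arm sizes. If enrolment has closed, it is enough to report how codes were released and that the block size was fixed.

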***Follow-up support***

A research assistant will be responsible for participants’ retention management and care support through WeChat and telephone (office hours: Monday to Friday from 8:00 am to 5:30 pm). Care support includes pre-test counselling, instruction of use of self-test kit, interpretation of results, advice for reactive test results, and other related emergency events. A log of each enquiry will be recorded.

***Follow-up on reactive self-tests***

Participants are advised to inform the research assistant if they have any reactive self-test results. Any participant with a reactive self-test result will be referred to undergo confirmatory laboratory testing and clinical examination at the designated clinics/ hospitals. The laboratory confirmation and management of participants with syphilis will be based on the standard protocols at the respective clinic. If the participants are diagnosed with syphilis, we will undertake further follow-up to obtain treatment information.

***Data collection***

**Syphilis testing record and results:** Confirmed syphilis self-testing will be determined by photo verification of the used test kit. Facility-based syphilis testing and result will be determined by photo verification of the test report. Participants in all three arms who upload photo verification will get 5 RMB (approximately equal to 0.7 US dollars).

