**Outcomes Measures**

The primary outcome is the proportion of participants who tested for syphilis during the trial. Syphilis tests may be either at a clinic or via self-test. This will be verified in all participants using photo-verification. We will additionally look at the incremental benefit of the lottery incentive efficacy in promoting syphilis, number of newly identified syphilis infections, the linkage to syphilis clinical care after self-testing, the proportion of HIV and other STIs (chlamydia, gonorrhea) tests among the participants who use self-testing and cost-effectiveness of syphilis self-testing in promoting uptake of syphilis testing among Chinese MSM.

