**Surveys**

**Baseline:** All participants complete a self-administered survey on an online survey platform (Wen Juan Xing, https://www.wjx.cn) at enrolment. The baseline survey includes questions on socio-demographic characteristics, sexual behaviors, past HIV/syphilis testing and treatment, and attitude towards syphilis self-testing.

**Follow-up surveys:** Participants in the three arms of the study will complete a brief online survey at three-monthly intervals. The follow up surveys collects information on the number, time, location, reasons for, and results of syphilis tests (including self-tests) and other STI tests at clinics and community sites, and sexual risk behaviors in the past three months. Participants in the two self-testing arms are also asked about the number of self-test kits they used to test their sexual partner(s) or if they gave any kits to someone else to test. At the last follow-up, participants will be asked to get STD (HIV, syphilis, chlamydia, and gonorrhea) screening test in their nearby clinic. The testing fee will be redeemed by an upload of the test results. Participants will be provided with 30 RMB (equal to 4 US Dollars) for their time to complete each follow-up survey.

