#### *Analysis plan*

Data will be retrieved from the online survey platform. De-identified datasets and codebook will be stored for statistical analysis. The syphilis testing proportion in each arm (control, standard self-testing, and lottery incentivized self-testing) will be assessed using an intention-to-treat analysis during the follow-up period, excluding confirmatory tests after a reactive self-test.

The effects of the intervention will be measured by comparing the differences in proportions of men who take syphilis testing during two rounds of follow up by using generalized estimating equation (GEE) model. We will use the chi-square test to compare differences in the proportion of linkage to syphilis clinical care, have HIV and other STI (chlamydia, gonorrhea) testing performed, and have condomless sex events with different partners within six months of randomization across three groups and use post-host test to check the significance of differences between each of the two groups.

We will estimate the total and incremental unit costs for each arm. All costs will be identified as start-up costs, fixed costs and variable costs. Start-up costs are incurred during the process of creating this study (e.g. survey platform coordination). Fixed costs are costs that do not change with an increase or decrease in the number of people served during the trial period (e.g. administration, office equipment). Variable costs are expenses that vary with the number of participants served (e.g. recruitment, supplies, postage fee). We will first calculate the total cost for each group, then divided these costs by the number of men tested and the number of newly identified syphilis cases detected in each study arm to obtain the incremental unit costs. In addition, we will build a decision tree model using a healthcare provider perspective to estimate the incremental cost for per additional person tested and case identified for each intervention will be calculated. Univariate, multivariate and probabilistic sensitivity analyses will be conducted to test the robustness of our results.

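### A photo of a used kit shows who received the kit, not who was tested, and the kit-sharing answers have no stated role in the primary outcome

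*Protocol*

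**What the plan says.** The Outcomes Measures section of the protocol defines the endpoint per man: "The primary outcome is the proportion of participants who tested for syphilis during the trial". It adds: "This will be verified in all participants using photo-verification". For self-tests, the Data collection section gives the rule: "Confirmed syphilis self-testing will be determined by photo verification of the used test kit". A facility test is confirmed by a photo of the test report. Each upload earns 5 RMB in all arms. In the lottery arm, a photo-verified test also earns a draw with a 10% chance of 100 RMB (Arms and Interventions, Table 1).

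Men in both self-testing arms may order up to one package a month for six months. The Surveys section asks these two arms about "the number of self-test kits they used to test their sexual partner(s) or if they gave any kits to someone else to test". The Analysis plan names one exclusion from the testing proportion: "excluding confirmatory tests after a reactive self-test".

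The Discussion concedes that "we cannot guarantee that submitted photographic proofs truly belongs to the patient". Its safeguard is: "To link self-test kits with the user, we will code each self-testing package", with the used strip photographed against that package.

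**The concern.** The endpoint concerns the participant's own test, but the evidence accepted for it is a used strip beside a coded package. A study kit used on a partner, photographed as instructed, meets the rule in full. The protocol foresees such use, because it asks about it. It does not say that such a photo fails to count, or that the survey answers will be set against the photos.

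The error runs mainly one way in the comparison with control, because only the two self-testing arms are sent free kits. Between those two arms it could differ, because the lottery arm has an extra reason to upload: a draw worth 0.10 × 100 = 10 RMB on average, on top of the 5 RMB paid to everyone. That is the comparison on which the 148 per arm is based.

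**Working it through.** **Inputs from the Sample size section.** Control 0.36 and self-testing 0.74 (pilot, one month); lottery 0.85; 80% power; type I error 0.05; 20% loss; 148 per arm.

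**The plan's own figures first.** Unpooled normal formula, two-sided: n = (1.96 + 0.842)² × [p₁(1−p₁) + p₂(1−p₂)] / (p₁−p₂)².

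- 0.36 v 0.74: 7.85 × (0.2304 + 0.1924) / 0.1444 = 23; 23/0.8 = 29. This matches the stated 29 per arm.
- 0.70 v 0.85: 7.85 × (0.21 + 0.1275) / 0.0225 = 118; 118/0.8 = 148. This matches the stated 148.
- 0.74 v 0.85: 7.85 × (0.1924 + 0.1275) / 0.0121 = 208; 208/0.8 = 260. This does not match.

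The standard-arm proportion behind the 148 is not stated, so both 0.74 and 0.70 are used below.

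**Assumption.** Let q be the share of men counted as tested whose every accepted photo shows another person's test. The documents give no value, so a range is shown. The recorded 0.74 is treated as the any-photo proportion.

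**Self-testing v control.** True self-testing proportion = 0.74 × (1 − q), with control left at 0.36:

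| q | Self-testing | Difference from 0.36 | Overstatement of 0.38 |
|---|---|---|---|
| 5% | 0.703 | 0.343 | 0.037 |
| 10% | 0.666 | 0.306 | 0.074 |
| 20% | 0.592 | 0.232 | 0.148 |
| 30% | 0.518 | 0.158 | 0.222 |

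To remove the contrast entirely, q = 1 − 0.36/0.74 = 0.51. At q = 10%, power with 118 evaluable men per arm (148 × 0.8) is still 0.998. If controls are misclassified too, the overstatement is 0.74·q(self-testing) − 0.36·q(control). With 10% and 5%, for example, it is 0.074 − 0.018 = 0.056.

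**Lottery v standard.** True difference = 0.85·(1 − q(lottery)) − p·(1 − q(standard)):

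| q standard | q lottery | p = 0.74 (recorded 0.11) | p = 0.70 (recorded 0.15) |
|---|---|---|---|
| 5% | 5% | 0.105 | 0.143 |
| 10% | 10% | 0.099 | 0.135 |
| 5% | 10% | 0.062 | 0.100 |
| 5% | 15% | 0.020 | 0.058 |

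Equal rates shrink the difference in proportion and do little harm. Unequal rates can matter.

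**The case against.** **The endpoint already means the participant's own test, and details may be left to an SAP.** The wording does refer to participants who tested, and an SAP might combine photos with survey answers. But this protocol itself fixes how a self-test is confirmed and names an exclusion, and neither touches sharing. The point therefore concerns a stated rule.

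**There are safeguards.** The coded package stops a photo of just any kit from being offered as a study kit. In all arms the survey also records the number, time and results of the man's tests, which could be checked against the photos. Both points stand. The code still cannot show who was tested, and no such cross-check is planned. The Discussion's remark about adjusting the analysis if necessary concerns controls who buy kits online, not sharing.

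**A reader might infer that only the self-testing arms are inflated.** The documents do not support that. The Discussion says controls may buy kits online, and another man's facility report could be uploaded in any arm.

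**A reader might infer that every shared kit biases the result.** It does not. The outcome is binary per man, so one who tests himself and also shares kits is classified correctly.

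**A reader might infer that most of a lottery benefit would be artefact.** That needs the last row of the second table: a threefold difference in q that nothing in the documents establishes, together with 0.74 v 0.85, which the 148 per arm does not match. A man holding a free kit can also earn the draw by testing himself, which argues against a large gap.

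**Conclusion.** The point holds in a limited form. Under the stated rule, a man whose only accepted photo shows someone else's test counts as tested, and data that could reveal this are collected without a stated use. Misclassification is possible, not shown, and its size is unknown.

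With an assumed q of 5% to 10% in the self-testing arm and none in control, the 0.38 contrast is overstated by 0.04 to 0.07. The conclusion against control is safe unless q approaches one half. Lottery versus standard is the more exposed comparison, but only if q differs between those arms. The ownership limitation is disclosed in the Discussion; disclosure does not change the rule. This is a cheap improvement, not a threat to the main comparison.

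**What to change.** 1. In Outcomes Measures and Data collection, state that a photo counts only if it shows the participant's own test.
2. Add an own-result declaration to each photo upload, for kit photos and facility reports alike, in all three arms.
3. In the Analysis plan, add a sensitivity analysis that uses the sharing answers and the self-reported tests. It would reclassify as untested any man whose only photographed kits were reported as used on or given to someone else, and it would be shown beside the any-photo result. State how men without a survey answer are handled.

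A rule that accepts a man only when his photos outnumber the kits he shared looks simple but should not be used. A man who tests himself, uploads one photo and gives two kits away would be scored as untested. The survey also asks whether kits were given away, not clearly how many, and the rule fails for men who skip the survey.

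**Cost.** One sentence in each definition, one tick box and one extra analysis of items already collected. The price is some reliance on self-report and possibly a slightly lower testing proportion. Recruitment began in December 2019 according to the Study design section, so earlier uploads would lack the declaration. The change should be dated, and the sensitivity analysis has to cover those uploads.
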